## 5.9 Informed Consent

Written informed consent will be obtained from all participants prior to recruitment. This will be taken by the study nurses within the CTRU of the Norfolk and Norwich University Trust Hospital.

## 5.10 Study Sequence

### 5.10.1 Study Procedure 1: *participant visit 1 ~ Screening Visit*

Once informed consent is obtained, clinical history and examination will be performed and eligibility criteria will be checked. Eligible participants will be recruited

to the trial. This procedure will take place between September and December 20~~1009~~. The following measurements will be performed:

- Skin Prick Allergy Test
- Routine biochemistry and haematology
- Total Nasal Symptom Scores
- Intranasal Allergen Challenge
- Spirometry (participants with asthma only)

Haematology will include haemoglobin, platelet count, white blood count and differential white blood count. Biochemistry will include renal function (Sodium, potassium, urea and creatinine) and liver function (albumin, bilirubin, alkaline phosphatase, alanine transaminase).

#### 5.10.2 Study Procedure 2: *participant visits 2, 3 and 4 ~ Baseline tests*

Procedure 2 will take place at least 2 weeks after procedure 1, and no later than December for isolated grass pollen allergy or November for participants with grass and tree pollen allergy. This procedure entails participant visits on two consecutive days with baseline measurements being taken initially (visit 2) and nasal samples being obtained at 6-8 hours (visit 3) from a subgroup of participants and at 24 hours (visit 4) from all participants after nasal allergen challenge.

The subjects will undergo a clinical examination. Baseline measurements will be the following:

- Total Nasal Symptom Scores
- Peak Nasal Inspiratory Flow (PnIF)
- Modified Intranasal Allergen Challenge
- Nasal lavage, nasal scrapings and peripheral blood
- Spirometry and asthma symptom scores (participants with asthma only)

Nasal lavage, nasal scraping and 20ml (approximately 4 teaspoons) peripheral blood will be obtained before and 24 hours after nasal allergen challenge. Nasal lavage will also be taken 30 minutes after allergen challenge and, in a subgroup, 6-8 hours after allergen challenge

- Characterisation of cells derived from nasal scrapings
- Epithelial and peripheral blood cell culture and analysis of TSLP, cytokines, chemokines and soluble cytokine receptors and sCD23 following *in vitro* allergenic challenge
- Eotaxin, MIP-1 $\alpha$  and RANTES in nasal lavage
- Differential counts of cells derived in nasal lavage and nasal scrapings

Participants with isolated grass pollen allergy will attend for procedure 2 no later than December 20~~1009~~.

#### 5.10.3 *Intervention and delivery schedule*

Participants will be randomised on a 1:1 ratio to receive probiotic or placebo formulation. Samples of the milk drinks, active or placebo, will be delivered by Yakult Europe B.V to IFR Norwich every 2 weeks. The samples will be HACCP certified for the safety of materials, production process and microbiological analysis (issued by TNO, Holland). The active and placebo drinks will be identical in composition except for inclusion of  $6.5 \times 10^9$  LcS organisms per 65ml of dairy drink. Volunteers will be supplied with probiotic or placebo milk drinks every 2 weeks throughout the 4-month intervention period. These samples will be distributed to the subjects by IFR Norwich.

#### 5.10.4 *Week -4 to 0*

Subjects will be asked to refrain from consuming any probiotic products from this point onwards for the course of the whole trial

#### 5.10.5 *Week 0*

Subjects will start a 4-month intervention period, consuming either active yoghurt-type drink or a similar placebo.

#### 5.10.6 Study Procedure 3: *participant visits 5, 6 and 7 ~ Post-intervention assessment*

This procedure will take place 4 months (16 weeks) after procedure 2 and no later than April for isolated grass pollen allergy or March for participants with grass and tree pollen allergy. Procedure 3 will entail participant visits on two consecutive days with nasal samples being obtained before (visit 5), at 8 hours (visit 6 for those able to return) and 24 hours (visit 7) for all participants following nasal allergen challenge. Subjects will be asked to refrain from taking anti-histamines for at least 3 days before this procedure.

Post-intervention measurements will be the following:

- Total Nasal Symptom Scores
- Peak Nasal Inspiratory Flow (PnIF)
- Modified Intranasal Allergen Challenge
- Spirometry (participants with asthma only)

Nasal lavage, nasal scraping and 20 ml (~4 teaspoons) peripheral blood will be obtained before and 24 hours after nasal allergen challenge. Nasal lavage will also be taken 30 minutes after allergen challenge and, in a subgroup, 6-8 hours after allergen challenge. These samples will be used for:

- Characterisation of cells derived from nasal scrapings
- Epithelial and peripheral blood cell culture and analysis of TSLP, cytokines, chemokines and soluble cytokine receptors and sCD23 following *in vitro* allergenic challenge
- Eotaxin, MIP-1 $\alpha$  and RANTES in nasal lavage
- Differential counts of cells derived in nasal lavage and nasal turbinates

#### 5.11 **Administration of active and placebo drinks**

Active and placebo drinks will be supplied as fermented milk in sealed pots of 65 ml with date stamped expiry. They should be stored at approximately 7 degrees Celsius (domestic **refrigerator**).

Fresh supplies of both products will be delivered to IFR Norwich every two weeks, and participants will receive delivery every two weeks from the institute.

#### 5.12 **Concomitant medication**

The following concomitant medications will be permitted providing sufficient 'wash-out' period is adhered to

- Intranasal cromolyn (2 weeks)
- Intranasal or systemic decongestants (3 days)
- Intranasal or systemic antihistamines (3 days)
- Antihistamines (3 days), except astemizole (6 weeks) or loratadine (10 days).

## 6 **Study procedures**

### 6.1 Skin prick testing

This test measures the presence of allergen-specific IgE attached to cells in the skin. It will be undertaken with a positive (histamine) and negative (saline) control and to common inhaled allergens. No antihistamines should be taken for 3 days hours before testing, except astemizole, which should not be taken within 6 weeks before testing and loratadine which should be withheld for 10 days. A droplet of allergen, histamine or saline will be placed onto the skin and the skin will be pricked with a lancet. Measurements of weal size will be recorded after 10 min (for histamine) and 15 min for allergens and control. A positive reaction will be one that is 2mm greater than the negative control.

### 6.2 Total Nasal Symptom Scores (TNSS)

Following exposure to allergen, there is an immediate rise in the reported symptoms. The magnitude of these symptoms changes with time, and the recording of the symptoms scored at various time points is referred to as the TNSS. Participants will be asked to record their symptoms on a 4 point scale, with 0 representing no symptoms and 3 representing maximal symptoms:

0 = absent symptoms (no sign/symptom evident)

1 = mild symptoms (sign/symptom clearly present, but minimal awareness; easily tolerated)

2 = moderate symptoms (definite awareness of sign/symptom that is bothersome but tolerable)

3 = severe symptoms (sign/symptom that is hard to tolerate; causes interference with activities of daily living and/or sleeping)

Symptoms will be recorded under the following;

- ~ Sneezing
- ~ Itching
- ~ Rhinorrhoea
- ~ Congestion

The individual symptoms will be summed to give a total nasal symptom score with a maximum value of 12 (Dreskin *et al.* 2002).

### 6.3 Asthma Symptom scores

Asthma symptom scores help to determine the severity of responses to inhaled allergens. Participants will be asked to record their symptoms on a 4-point Likert scale, where symptoms will be scored as follows;

- 0 = none
- 1 = mild
- 2 = moderate
- 3 = severe

Symptoms will be recorded under the following:

- Cough
- Wheeze
- Breathlessness

#### 6.4 Peak Nasal Inspiratory Flow (PnIF)

Peak nasal inspiratory flow is an easy and inexpensive means of measuring nasal obstruction and correlates significantly with severity of symptoms scores. Nasal inspiratory flow will be measured using an In-check™ flow meter (Clement Clarke International Ltd, Harlow, UK). After blowing their nose, participants will inspire forcefully from residual volume to total lung capacity with their mouth closed. All measurements will be made while in the sitting position with a good seal around a purpose built facemask. The median of 3 readings will be recorded.

#### 6.5 Intranasal allergen challenge

In seasonal pollen-related disease, there are variations between subjects in the extent of pollen sensitization. We are using an out-of-season nasal allergen challenge in order to control variability and focus on allergic disease mechanisms. Subjects will be asked to refrain from anti-histamine use for at least 3 days leading up to the Day 1 assessments. The procedure will be performed as previously described (Dreskin *et al.* 2002). Briefly, baseline nasal symptoms scores will be recorded. Saline will be administered 1 squirt up each nostril and the symptom scores will be recorded again after 5 minutes. Allergen will be administered to the nose in ten-fold escalating doses of grass pollen from 10 to 1000bau (given as 0.1ml of concentrations from 100 to 10,000 biologically active units (bau)/ml) every 5 minutes. Symptom scores will be recorded 5 minutes following each dose. The challenge will finish when the participant has a TNSS of 4 or the highest concentration has been given.

#### 6.6 Modified Intranasal allergen challenge

Nasal allergen challenge is a non-invasive method used to study pathophysiological mechanisms in rhinitis. Normally a single high dose of allergen is sprayed into the nose to induce an allergic response. We have modified this test so that we will first find an optimum dose that will induce a certain fixed level of response for each participant. That individual dose will then be used in the study. We believe this will avoid any adverse events and will improve our study since all participants will start the study at the same maximum response. Changes from this will be monitored following intervention.

Subjects will be asked to refrain from anti-histamine use for at least 3 days leading up to the Day 1 assessments. A modified challenge will be performed (Dreskin *et al.* 2002). The concentration of allergen identified in the allergen challenge performed during procedure 1 (screening visit) will be administered at 0.1ml using a pump spray. Nasal symptoms (based on a combination of nasal symptoms including nasal obstruction, itching, sneezing, and rhinorrhoea) will be recorded at 10 minutes, 30 minutes then hourly for 12 hours. PnIF will be measured prior to allergen challenge 10 minutes, 30 minutes, and hourly for 12 hours.

#### 6.7 Spirometry

Spirometry will be used to monitor the severity of asthma, and participant response to treatment. This is performed using a spirometer which is a device which measures the amount of air that you can blow out. A spirometry reading usually shows one of four main patterns:

- Normal
- An obstructive pattern – as in asthma
- A restrictive pattern
- A combined obstructive / restrictive pattern

Spirometry will be performed with a Microlab spirometer (Micro Medical Ltd, Rochester, Kent, UK). The procedure will be performed according to American Thoracic Society specifications [1987]. Measurements will be made of FEV1, FVC, FV6 and peak expiratory flow.

## 6.8 Laboratory measurements

Cells derived from nasal scrapings, peripheral blood and their secretions will be tested for key markers of allergic inflammation and its regulation. This will enable us to measure efficacy of the intervention.

- Characterisation of cells derived from nasal scrapings
- Epithelial and peripheral blood cell culture and analysis of TSLP, cytokines, chemokines and soluble cytokine receptors and sCD23 following *in vitro* allergenic challenge
- Eotaxin, MIP-1 $\alpha$  and RANTES in nasal lavage
- Differential counts of cells derived in nasal lavage/turbيناتes

## 6.9 Nasal tissue collection

### 6.10.1 Nasal scraping

Scrapings of nasal epithelium (near the inferior turbinate) will be obtained from all subjects with a Rhino-probe (Arlington Scientific, Springville, UT) according to manufacturer's instructions. Two contiguous scrapings will be taken from the right nostril on Day 1 prior to allergen challenge. Two additional scrapings will be collected from each subject on Day 2 approximately 24 hours after challenge. The first scrape will be from the left nostril the second scrape will be from the right nostril

### 6.10.2 Nasal lavage

This will be performed according to the method described by Grünberg *et al.* (1997). Briefly, a Foley silicone catheter size number 14, is prepared by cutting off the tip of the catheter just distal to the balloon while keeping the balloon intact (about 5 mm from the end) and also cutting off the opposite end of the balloon that does not inflate it, until it will fit into a 10 ml syringe. The tip of the Foley catheter will be located in the right frontal nasal passage (around 1 or 1.5 cm in; not against nasal septum) and the subject will hold the catheter to keep it in position. The balloon will then be inflated until it feels tight but does not hurt. The subject will sit at a desk in the writing position. The technician will instil 10 ml of isotonic saline (0.9%) through the catheter leaving the syringe on the catheter. If fluid comes out of the nostril in which the balloon is blown up, the procedure will be repeated with the balloon inflated more. If fluid comes out of the nostril in which there is no balloon, it will be allowed to drip into the container and the head will be tilted to the side of the balloon catheter. The fluid will be instilled and withdrawn 20 times over a 5 minute period. Then, the balloon will be deflated.

### 6.10.3 Nasal scraping processing

Cells that are not for culture will be placed in phosphate buffered saline and centrifuged at 1000rpm (140g) for 10 minutes. Cells will be resuspended in 4% paraformaldehyde in PBS, pH 7.4 for 10 minutes. The fixed cell suspension is centrifuged (1000rpm, 5 minutes) and resuspended at  $1 \times 10^6$ /ml in sterile PBS; 100 $\mu$ l aliquots are then loaded into cytopsin funnels and centrifuged onto microscope slides pre-coated with adhesive using a cytopsin centrifuge at 600rpm (30g) for 5 minutes.

## 6.10 Preparation of grass pollen antigens for in vitro challenge

Grass pollen antigens used for the nasal allergen challenge be the same as those used for the nasal allergen challenge, or they may be purchased as grass mixes from Pharmacia Diagnostics (Sweden). The allergen will be at pre-determined at its optimum dose.

#### **6.11 Preparation of mononuclear cells(MNC) and cell culture**

Heparinised peripheral blood will be diluted 1:1 with Hank's Balanced Salt Solution (HBSS) and the MNC isolated by density gradient centrifugation using Ficoll-Isopaque (Sigma, Dorset, UK). Following 3 washes with HBSS, the cells will be resuspended in tissue culture medium (TCM) comprising RPMI 1640 medium, 2mmol L-Glutamine, 100ug each of penicillin and streptomycin (all from Sigma) and 5% autologous plasma. Cell concentrations will be adjusted to  $2 \times 10^6$ /ml prior to culture in the presence or absence of pollen allergen at optimum dose. Following culture for 6 days, supernatants will be collected and stored at  $-80^{\circ}\text{C}$  to await analysis.

#### **6.13 Preparation and *in vitro* culture of nasal epithelial cells**

Specimens of nasal turbinates will be taken and washed immediately in RPMI 1640 medium containing 50 mg/ml gentamycin and 20 mM L-glutamin. The epithelium will be detached mechanically from the lamina propria and digested overnight at  $4^{\circ}\text{C}$  in trypsin solution (0.17%). After disaggregation of the cells, they will be washed in bronchial epithelial growth medium (BEGM; Promocell, Heidelberg, Germany). The cells will be pelleted at 125 g at room temperature for 5 min and resuspended in growth medium. The nasal cells will then seeded at a density of  $5 \times 10^3$  on uncoated polystyrene culture dishes of 10 cm diameter. Cultures will be maintained at  $37^{\circ}\text{C}$  with 5%  $\text{CO}_2$  in air. The cells will be fed with fresh pre-warmed media after 48 h and later every second day. When the cells reach about 75% confluency they will be detached by trypsin digestion (0.5g trypsin and 0.2g EDTA) divided and passaged until use.

#### **6.14 Analysis of culture supernatants**

##### **6.14.1 Grass pollen-specific serum IgE and IgG**

Within two hours of blood collection, coagulated blood will centrifuged at  $4^{\circ}\text{C}$  to stimulate clot retraction and to give a good serum yield. Once collected, the serum will be stored at  $-80^{\circ}\text{C}$  until immunoglobulin (Ig) analysis is performed. Grass pollen-specific IgE levels will be identified using either the RIDA-screen system from R-Biopharm (Quadrantech, Surrey, UK.) or the Pharmacia ImmunoCap system. Quantification of these levels, in standard units, will be performed using the appropriate instrumentation and software.

##### **6.14.2 *FcεR1* expression on plasmacytoid Dendritic Cells (pDCs)**

Cells will be cultured for 6 days in the presence or absence of grass pollen antigens, washed and stained using established techniques. pDCs will be identified with fluorochrome-labelled antibodies for their CD123+, CD303+ and CD11c- phenotype. Their co-expression of *FCεR1* will be evaluated using a compatible fluorochrome-labelled antibody in a 4-colour staining procedure, followed by flow cytometry.

##### **6.14.3 Cytokines and chemokines**

These will be detected using bead array technology and flow cytometry. The assay is based on a series of spectrally discrete particles that can be used to capture and quantify soluble analytes. The analyte is then measured by flow cytometry. Concentration of the unknowns is calculated through the use of standards. The following cytokines will be measured; IL-1, -4, -5, -6, -8, -10, -12p70, -13, IFN- $\gamma$ , TNF $\alpha$ , Rantes, Eotaxin, MIP-1a and TGF- $\beta$ .

#### 6.14.4 Soluble CD23

Serum sCD23 will be measured by ELISA according to the manufacturer's instructions.

### 6.15 Analysis of cultured nasal epithelial cells

#### 6.15.1 Cellular expression of co-stimulatory molecules CD80, CD86, OX40L and CD117

Using 5-colour immunofluorescent staining, cell lineage will be defined using lineage-specific reagents. At the same time their co-expression of CD80, CD86 and OX40L will be analysed using compatible fluorochrome-labelled antibodies and flow cytometry.

#### 6.15.2 Cell surface expression of CD117, IgE, intracellular tryptase and chymase

Cell surface and intracellular expression will be analysed using fluorochrome-labelled antibodies and flow cytometry. Intracellular antigens will be detected by prior cell permeabilisation according to the standard in-house method.

#### 6.15.3 Presence of Soluble Cytokine Receptors (SCR) in culture supernatants

SCR will be determined by bead array technology (Millipore, UK) according to the manufacturer's instructions.

## 7 Adverse Events and Serious Adverse Events

The local investigator at the study site is responsible for the detection and documentation of events meeting the criteria and definition of adverse events or adverse reactions including reporting to the sponsor.

7.1 "adverse event" (AE) means any untoward medical occurrence in a subject to whom a medicinal product has been administered, including occurrences which are not necessarily caused by or related to that product.

7.1.2 "adverse reaction" (AR) means any untoward and unintended response in a subject to an investigational medicinal product, which is related to any dose administered to that subject.

7.1.3 "serious adverse event" (SAE) or "serious adverse reaction" (SAR) or "unexpected serious adverse reaction" means an adverse event/reaction that fulfils at least one of the following criteria:

A) Results in death

B) Is life-threatening

NOTE: The term 'life-threatening' in the definition of 'serious' refers to an event in which the subject was at risk of death at the time of the event. It does not refer to an event, which hypothetically might have caused death, if it were more severe

C) Requires hospitalisation or prolongation of existing hospitalisation

NOTE: In general, hospitalization signifies that the subject has been detained (usually involving at least an overnight stay) at the hospital or emergency ward for observation and/or treatment that would not have been appropriate at the GP clinic or out-participant setting. Complications that occur during hospitalization are AEs. If

a complication prolongs hospitalization or fulfils any other serious criteria, the event is serious. When in doubt as to whether “hospitalization” occurred or was necessary, the AE should be considered serious. Hospitalization for elective treatment of a pre-existing condition that did not worsen from baseline is not considered an AE.

D) Results in persistent or significant disability or incapacity or

NOTE: The term disability means a substantial disruption of a person’s ability to conduct normal life functions. This definition is not intended to include experiences of relatively minor medical significance such as uncomplicated headache, nausea, vomiting, diarrhoea, influenza, and accidental trauma (e.g. sprained ankle) which may interfere or prevent everyday life functions but do not constitute a substantial disruption.

E) Consists of a congenital anomaly or birth defect

F) Medical or scientific judgement should be exercised in deciding whether reporting is appropriate in other situations, such as important medical events that may not be immediately life-threatening or result in death or hospitalization but may jeopardize the subject or may require medical or surgical intervention to prevent one of the other outcomes listed in the above definition. These should also be considered serious. Examples of such events are invasive or malignant cancers, intensive treatment in an emergency department or at home for allergic bronchospasm, blood dyscrasias or convulsions that do not result in hospitalization, or development of drug dependency or drug abuse.

- 7.1.4 “unexpected adverse reaction” means any adverse reaction, the nature or severity of which is not consistent with the applicable product information (e.g. investigator’s brochure for an unapproved investigational product, or summary of product characteristics [Smock] for an authorised product).
- 7.1.5 Severity: The term “severe” is used to describe the intensity of a specific event. This is not the same as “serious” which is based on participant/event outcome, or action criteria.]
- 7.1.6 “Suspected Serious Adverse Reaction (SSAR)”  
Means an adverse reaction that is classed in nature as serious and which is consistent with the information about the medicinal product
- 7.1.7 “Suspected Unexpected Serious Adverse Reaction (SUSAR)”  
means an adverse reaction that is classed in nature as serious and which is not consistent with the information about the medicinal product in question
- 7.1.8 Clinical Laboratory Abnormalities and Other Abnormal Assessments  
Abnormal laboratory findings (e.g., clinical chemistry, haematology) or other abnormal assessments that are judged by the investigator as **clinically significant** will be recorded as AEs or ARs if they meet the definition’s above. Clinically significant abnormal laboratory findings or other abnormal assessments that are detected during the study or are present at baseline and significantly worsen following the start of the study will be reported as AEs or ARs. However, clinically significant abnormal laboratory findings or other abnormal assessments (eg spirometry, PnIF) that are associated with the disease being studied, unless judged by the investigator as more severe than expected for the subject’s condition, or that are present or detected at the start of the study and do not worsen, will not be reported as AEs or ARs. The investigator will exercise his or her medical and

scientific judgment in deciding whether an abnormal laboratory finding or other abnormal assessment is clinically significant.

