Procedure 2 involves participant visits on two consecutive days. This will involve nasal samples being obtained before and 24 hours after the nasal allergen challenge. At the first of the 2-day procedure (visit 2), participants will have a clinical examination, and baseline nasal and total allergic rhinitis symptoms scores, nasal peak inspiratory flow, nasal scrapings and nasal lavage. 20ml blood will be taken for laboratory analysis. They will then undergo a nasal allergen challenge and record their nasal symptoms and peak nasal inspiratory flow at 5 mins, 30 mins then hourly for 12 hours. A nasal lavage will be collected at 30 mins. Asthmatic participants will undergo spirometry prior to and 1 hour following the nasal allergen challenge. They will also record asthma symptom scores prior to the challenge and hourly following the challenge. Those participants able to return after 6-8 hours (visit 3) to give a nasal lavage, peak nasal inspiratory flow (PNIF) and asthma symptom scores (ASS) and spirometry in asthmatic participants. These subjects will form a subgroup. All participants will return for the 24 hours later (visit 4) following the nasal allergen challenge, for a second nasal scraping and lavage. 20 ml peripheral blood will be taken at this time for laboratory analysis. Following this, participants will be randomized to active drink or similar placebo daily for 4 months. Procedure 2 will take place at least 2

weeks after procedure 1 and no later than November. Participants with isolated grass pollen allergy will attend for procedure 2 no later than December 20~~10~~.

Procedure 3: Post-intervention follow-up measurements ~ participant visits 5, 6 and 7

Procedure 3 involves participant visits on two consecutive days when they will undergo follow-up assessment identical to procedure 2. Procedure 3 will take place 4 months following procedure 2 and no later than March 201~~0~~. Participants with isolated grass pollen allergy will attend for procedure 3 no later than April 201~~0~~.

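### Section 7.1.8 names spirometry in the disease-related exemption from adverse event reporting, so a non-serious fall in lung function after the allergen challenge can be left out if judged expected

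*Protocol*

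**What the plan says.** Section 7.1.8 starts from a general rule. Clinically significant abnormal results that appear during the study, or that are "present at baseline and significantly worsen following the start of the study will be reported as AEs or ARs".

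The next sentence makes an exception with two limbs. The first opens "However, clinically significant abnormal laboratory findings or other abnormal assessments (eg spirometry, PnIF) that are associated with the disease being studied", and it lapses only "unless judged by the investigator as more severe than expected for the" subject's condition. The second covers findings that were there at the start and have not worsened. Results under either limb "will not be reported as AEs or ARs".

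On spirometry itself:

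- Section 5.1 (Procedure 2): "Asthmatic participants will undergo spirometry prior to and 1 hour following the nasal allergen challenge". It adds a reading at 6–8 hours in the subgroup able to return, and it makes Procedure 3 identical to Procedure 2.
- The schedule in Section 5.2 marks spirometry at 0, 8 and 24 hours of both procedures, for asthmatic participants only.
- Section 6.7: "Spirometry will be used to monitor the severity of asthma, and participant response to treatment".
- Section 8 lists the primary and secondary endpoints. Spirometry is not among them; the 12-hour area under the curve for PnIF is.

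Section 7.1.3 F gives, as an example of a serious event, "intensive treatment in an emergency department or at home for allergic bronchospasm".

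**The concern.** The exemption treats two unlike measurements alike. A drop in PnIF is the response that the challenge is designed to produce and the trial is designed to reduce; reporting every such drop as an adverse event would add nothing. A drop in FEV1 in an asthmatic participant is an unintended lower-airway reaction to a study procedure. The sentence does not separate such a provoked fall from background disease, and it gives no reference value for what is expected.

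What is at stake is the completeness of the AE tables, not the efficacy result. Section 6.6 expects the individually chosen challenge dose to avoid adverse events, and that dose is given at Procedure 2 and again at Procedure 3. The AE record is the natural place to check that expectation in asthmatic participants, and the exemption thins it at that point.

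**Working it through.** No arithmetic bears on the wording itself. The check is to follow one result through the text: a clinically significant, non-serious fall in FEV1 one hour after the challenge in an asthmatic participant.

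1. **General rule of 7.1.8.** The fall was detected during the study and is a significant worsening from the pre-challenge reading. On this sentence alone it is reported.

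2. **First limb of the exception.** Is it associated with the disease being studied? That disease is seasonal allergic rhinitis (synopsis; Section 3). Asthma is a comorbidity and a stratification factor (Section 5.4). Read strictly, a lower-airway fall is outside the limb. But the sentence names spirometry as an example, and spirometry is done only in asthmatics. A site will reasonably conclude that asthmatic lung-function findings are meant to be inside it.

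3. **Test that restores reporting.** The condition that a finding has not worsened belongs only to the second limb. The first limb has no worsening test. Its single safeguard is the investigator's view of what is expected for that subject, with no threshold or reference reading.

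4. **Other routes into the safety record.** Section 7.1.3 F reaches bronchospasm that needed intensive treatment. Section 7.1.9 requires prompt reporting of serious events related to study participation, including protocol-mandated procedures. A non-serious fall meets neither. AE reporting is its route, and step 2 can close that route.

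5. **Other measurements after the challenge.** PnIF is objective but nasal, and it is named in the same exemption. Asthma symptom scores are taken hourly, but they are subjective. Spirometry (FEV1, FVC, FV6 and peak expiratory flow, Section 6.7) is the only scheduled objective lower-airway measure.

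**How many readings could be involved.** After each challenge an asthmatic participant has readings at 1 hour (Section 5.1) and 24 hours (schedule table), plus one at 6–8 hours in the subgroup. That is 2 to 3 per challenge and, over Procedures 2 and 3, 2 × 2 = 4 to 2 × 3 = 6 per asthmatic participant. These are opportunities, not events. A reading is affected only if it is abnormal, clinically significant, taken to be disease-associated, and judged no worse than expected. The protocol gives neither the number of asthmatics among the 60 participants nor a rate for such falls, so no count of affected participants can be derived.

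**The case against.** The strongest reply is that only a label is at stake. Spirometry is a scheduled measurement, so the values are collected whatever 7.1.8 says, and asthma symptom scores are collected beside them. The exemption is conditional, and serious events are reported regardless. All of that stands, and it rules out several stronger readings that a reader might draw:

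- *That such falls go unrecorded.* The text removes AE/AR reporting, not the measurement. The Procedure 2 values exist before Procedure 3 takes place.
- *That spirometry is the only objective respiratory safety signal.* PnIF is objective too. The supportable statement is confined to the lower airway.
- *That 7.1.8 contradicts 7.1.3 F.* One deals with test results, the other with when a clinical event is serious. Intensively treated bronchospasm is reportable under both readings of 7.1.8.
- *That 7.1.8 contradicts its own preceding sentence.* A rule followed by an exception is not a contradiction; the question is whether the exception is drawn in the right place.
- *That every asthmatic participant is affected at each reading.* Several conditions must all be met first.

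Two further replies have less force. If the disease is rhinitis, a fall in FEV1 may already lie outside the exemption; but naming spirometry points the other way, and sites could differ. Section 6.7 also gives spirometry a role in following response to treatment, and Section 9 allows similar models for other response variables. That may make it an exploratory outcome. It does not make a provoked lower-airway fall an intended response, as a fall in PnIF is.

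Finally, the amended text would still rest on the investigator's judgement of clinical significance. That is true. The amendment removes the second, looser judgement about what was expected; it does not remove judgement altogether.

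**Conclusion.** The point holds as a gap in reporting rules. As written, 7.1.8 lets a clinically significant, non-serious spirometry fall provoked by the challenge be left out of AE reporting when the investigator regards it as expected, and no other provision of Section 7 requires it to be reported. This rests on reading the named example as bringing asthmatic lung-function findings within the exemption. On the stricter reading the clause is ambiguous rather than permissive, and the same edit settles it.

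The consequence is modest. It concerns asthmatic participants only, in unknown number, and a subset of their post-challenge readings. It does not touch the primary endpoint or its analysis. It is a cheap improvement to the completeness of the safety record, not a fault that undermines the trial.

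**What to change.** In Section 7.1.8, delete spirometry from the parenthesis and limit the disease-associated exemption to nasal symptoms and PnIF. Add one sentence: a clinically significant worsening of spirometry after the challenge, relative to the pre-challenge value on the same day, is reported as an adverse event.

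The change is to one paragraph, uses readings already scheduled, and alters no dose, procedure or treatment rule. The cost is a few more AE forms.
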